### Outcome measurements

Outcomes measurements will be assessed at baseline, at week 4, at week 8 and at the 12th week follow-up. The DAS28 joints will be assessed for swelling and tenderness by a trained staff member. All the outcome assessments will be accomplished by the same staff researcher.

The primary outcome measure will be ACR20 criteria [11] by week 8. To achieve ACR20, a patient must have a 20% or greater reduction in the number of both tender and swollen joints and a 20% or more improvement in 3 or more of the following: the physician’s or patient’s assessment of global health status, the patient’s assessment of pain on a visual analogue scale, the patient’s assessment of function using a modified version of the Health Assessment Questionnaire (HAQ), and the erythrocyte sedimentation rate (ESR) or serum C-reactive protein (CRP) level.

Secondary outcome measures will include: ACR20 assessed at week 4, ACR50 criteria assessed at weeks 4 and 8, changes at weeks 4 and 8 in DAS28, and joint synovitis classification. Since the DAS28 is a combined index to measure the disease activity in patients with RA, it can be used in combination with the European League Against Rheumatism response criteria [10]. In the present trial, the DAS28 score will be calculated, based on either the C-reactive protein (DAS28-CRP) or the erythrocyte sedimentation rate (DAS28-ESR) [10]. Changes in joint synovitis classification will be determined by serial musculoskeletal ultrasound (MUSU) focused on the total sum of synovitis classification based on the joint used gels. The MUSU synovitis classification will derive from each MUSU measurement as follows: 0 level, no doppler synovial tissue signal; level 1, three independent points or 2 successive or 1 to 2 independent dot doppler synovial tissue signals; level 2, doppler signal indicating <50% of the area representing synovium; level 3, doppler signal indicating synovium in >50% of the measured area [12].

The safety evaluation will be accomplished by a face-to-face interview at the 4th and 8th weeks and by a a telephone-interview with the remote 12th week follow-up. Adverse experiences of interest will include: manifestations of cutaneous allergy (erythema, edema, itching) and gastrointestinal stimulation due to mucous membrane damage. In addition, because of the high frequency of reproductive system damage, the safety evaluation will focus on changes in menstruation patterns among premenopausal female participants. The relevant female participants will be asked a general question about whether they have observed any change in their menstruation pattern. Irrespective of how they answer that question, a series of follow-up questions will attempt to quantify any change in the menstrual cycle (extension, shortening or no change), or in the quantity of menstrual flow (increased, reduced, or unchanged). Blood and urine routine laboratory examinations, including glutamic-pyruvic transaminase, glutamic oxalacetic transaminase, creatinine and urea nitrogen will be accomplished at baseline and on the 8th week. Quantitative changes will be addressed on the record. Professional judgments regarding the severity of any given adverse effect and any recognized relationship between the adverse effect and the study interventions will be documented if any of the above safety measures are observed to fall beyond normal clinical or laboratory ranges.

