### Intervention

The ingredients for the compounding of the topical TwHF gel include: Tripterygium wilfordii Hook F, Mangxiao (Mirabilite), Chuanxiong (Rhizoma Ligustici), Ruling (Olibanum), and Moyao (M yrrh) (proportions: 4:4:2:2:1). The topical placebo gel is made of a viscous agent and sucrose which make it looks like the active preparation. Both of the gels will be prepared by the Pharmaceutical Department of Guang’anmen Hospital, and the herbs will be purchased from Beijing Fengtaijinyuan Pharmaceutical Co., Ltd. Each gel is 20 gram (g) per tube. Both the topical compound TwHF gel and the placebo gel will be applied for 1st to 5th metacarpophalangeal joints, 1st to 5th proximal interphalangeal joints, wrists, knees and ankles 10 g for 1 h, once a day from week 0 through week 4 and 10 g from week 5 through week 8.

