## Discussion

To date, only a small number of studies have documented the effectiveness of CET using any pharmacological agent. This clinical trial is designed as a double-blinded, randomized, controlled study of TwHF-based CET in a moderate active RA population with 8 weeks of observation. Considering the main clinical features of active RA to be joint swelling, tenderness, and pain, these are the clinical manifestations monitored using validated instruments. It is anticipated that topical compound TwHF gel will also be effective in controlling the clinical manifestations of RA and safe for use by RA patients.

In animal studies, TwHF microemulsion has been observed to imeliorate the severity of a murine adjuvant-induced arthritis model and to reduce the male reproductive toxicity and hepatotoxicity [14]. It is hoped that the topical use of TwHF as a clinical application of CET in RA patients will be found to be both safe and efficacious. Although TwHF and its extracts have shown good responses in patients with RA it is currently limited to use in elderly patients because of demonstrated reproductive toxicity. Safety observations from previous studies have shown that compound TwHF applied topically can cause cutaneous reactions which are reversible with discontinuation of the topical TwHF compound. In addition, increases in serum aminotransferase and alterations in menstruation among female patients have been reported [5, 6].

There are several aspects of the current study design that are different from previous CET clinical studies using this agent. Firstly, the design of dosage adjustment in this study will demonstrate whether the period of dosage reduction will bring additional benefits to the patients. In clinical practice, patients often continue to apply the effective medicine for an additional period in order to consolidate the efficacy, though there is no evidence to support this practice. Secondly, the follow-up assessment has rarely been included in CET research. Since oral preparations of THwF have often exhibited side effects, such as gastrointestinal and menstrual disorders, special emphasis has been placed upon an 4-week follow-up (to monitor at least one menstrual cycle).

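### One researcher makes all outcome assessments, and nothing stated shields the joint counts, physician global or ultrasound grades from skin reactions that could reveal the active gel

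*Protocol article*

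**What the plan says.** In the protocol article, the Outcome measurements section gives joint counting to a trained person ("The DAS28 joints will be assessed for swelling and tenderness by a trained staff member") and then adds: "All the outcome assessments will be accomplished by the same staff researcher". ACR20, the primary outcome at week 8, requires improvement in both the tender and the swollen count. It also requires improvement in three or more further items, one of which may be the physician's global assessment. The Doppler synovitis grade, summed over the gel-treated joints, is a secondary outcome in the same section.

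Safety appears under the same heading and falls in the same weeks as the efficacy assessments: "The safety evaluation will be accomplished by a face-to-face interview at the 4th and 8th weeks". Redness, swelling and itching of the skin are listed as events of interest. The person who conducts the interview is not named.

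The Intervention section has the gel "applied for 1st to 5th metacarpophalangeal joints, 1st to 5th proximal interphalangeal joints, wrists, knees and ankles". The Discussion says of earlier experience that "compound TwHF applied topically can cause cutaneous reactions which are reversible with discontinuation". The Blinding section relies on sealed envelopes, identical packing and numeric codes. The placebo, a viscous agent with sucrose, is described as matching the active gel in appearance.

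**The concern.** The stated blinding measures protect the allocation code and the look of the product. They do not protect against an assessor inferring the arm from a side effect. Here the side effect is visible, is reported for the active compound, and would appear on skin that the assessor has to examine.

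Both joint counts are matters of judgement and both are mandatory for ACR20, so an assessor who suspects active treatment can move the primary outcome. The direction is not fixed. Expectation could raise the active-arm response, while skin oedema over a small joint that is scored as joint swelling could lower it.

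The ultrasound grade is the outcome best suited to serve as a check on the clinical findings. If the same person grades it knowing the skin or clinical findings, it can carry the same expectation and no longer corroborates ACR20 independently.

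**Working it through.** The plan gives no figure on this point, so there is none to reproduce. The check has two parts.

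**1. What the text supports**

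| Link in the argument | Basis | Status |
|---|---|---|
| One person makes all outcome assessments | Outcome measurements | Stated |
| That person scores joints, physician global and ultrasound | Literal reading of the word all | Follows from the wording; not itemised |
| That person also conducts the safety interview | Same heading, same weeks | Possible; no interviewer is named |
| The active compound can cause skin reactions | Discussion | Stated, without a rate |
| The gel lies on the scored joints | Intervention | Largely; the ankles are treated but are not among the 28 joints |
| The ultrasound grader knows the visit, skin or clinical findings | None | Not stated either way |

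The risk to the joint counts does not depend on the third row. Whoever palpates a treated joint sees a reaction on it.

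**2. Scale, under assumptions**

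From the plan (Sample size): 84 per arm, planning ACR20 rates of 34.3% (active) and 12.5% (placebo), significance level 0.05, taken as two-sided. Assumed, because the documents give nothing: 10% to 30% of active and 3% of placebo patients show or report a reaction, and unmasking shifts ACR20 by 10 to 20 percentage points in those patients.

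Bias in the group difference = (reaction rate, active − reaction rate, placebo) × shift:

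- Low: (0.10 − 0.03) × 0.10 = 0.007, or 0.7 points.
- High: (0.30 − 0.03) × 0.20 = 0.054, or 5.4 points.

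The planned difference is 34.3 − 12.5 = 21.8 points, so this is about 3% (0.7/21.8) to 25% (5.4/21.8) of it.

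Type I error with a true rate of 12.5% in both arms and an upward bias b: set p_a = 0.125 + b and p̄ = (p_a + 0.125)/2. Then s0 = √[2p̄(1 − p̄)/84] and s1 = √[(p_a(1 − p_a) + 0.125 × 0.875)/84]. The error is Φ[(b − 1.96·s0)/s1] + Φ[(−b − 1.96·s0)/s1].

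| b (points) | s0 | s1 | Two-sided type I error |
|---|---|---|---|
| 0.7 | 0.0516 | 0.0516 | 5.2% |
| 2 | 0.0527 | 0.0527 | 6.7% |
| 3 | 0.0535 | 0.0535 | 8.6% |
| 5 | 0.0551 | 0.0550 | 14.8% |
| 5.4 | 0.0554 | 0.0552 | 16.3% |

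Exact binomial enumeration at 2, 3 and 5 points gives 6.5%, 8.5% and 14.6%.

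A second set of assumptions leads to the same conclusion. Let a share f of active patients react and let a non-responder among them be scored as a responder with probability g. The bias is then 0.875·f·g. With f = 5% and g = 10% it is 0.4 points (error 5.1%). With f = 10% and g = 25% it is 2.2 points (7.0%). With f = 20% and g = 25% it is 4.4 points (12.6%). The result is driven by inputs that the documents do not supply.

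**The case against.** A single assessor is a defensible choice: it removes variation between raters and does not in itself break the blind. The gels are coded, identically packed and alike in appearance, and the allocation is withheld from staff. Of the additional ACR20 items, only the physician global is scored by the assessor; the others are patient-reported or laboratory values. The placebo is also a gel with unknown skin effects, and patients with skin allergy or broken skin at the treated sites are excluded. A fuller operating procedure, not shown, may cover image handling. All of this stands, and it limits how much can be claimed. It does not remove the risk, because both joint counts are mandatory and none of the stated safeguards acts on side effects.

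Three stronger readings are tempting but not supported:

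- A reader might infer that the assessor certainly asks about skin reactions. No interviewer is named, and the Abstract lists safety apart from the efficacy outcomes and bases it on spontaneous complaints.
- A reader might infer that ultrasound is graded with the skin, clinical scores and visit known. The article does not say what the grader knows or in what order images are read.
- A reader might infer that knowledge of visit order biases the treatment comparison. Such drift would act on both arms and largely cancel between them. It would affect mainly the planned within-arm tests.

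**Conclusion.** The concern holds in limited form. The article gives all outcome assessments to one person and describes nothing that separates the subjective scores from visible or reported skin reactions to the active gel. Bias in the joint counts, the physician global and the ultrasound grades is plausible, in either direction.

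Its size cannot be set from the documents. Under the assumptions above it runs from negligible (0.7 points, type I error about 5.2%) to several percentage points (5.4 points, about 16%). The type I error figures assume an upward bias and more reactions in the active arm; a downward bias would instead hide part of a true effect. The documents do not show that the blind will be broken or that ACR20 will be inflated. This is a cheap improvement to the plan, not a flaw that invalidates it.

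**What to change.** Keep the single assessor and add two rules to the sentence on outcome assessment.

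1. At each visit, record and lock the patient-reported items, then the joint counts and physician global, before the safety and menstrual interview begins. Patients stay free to report adverse effects at any time. A rule to withhold them would conflict with the Abstract's reliance on spontaneous complaints.
2. Store the Doppler ultrasound images under a code. Grade them after the patient's last visit, in random order, without visit label, skin findings or clinical scores. The same researcher can do this.

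The article should also say who conducts the safety interview.

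Cost: one paragraph in the operating procedure, image storage and a later reading session, with no extra staff, visits or procedures. Ultrasound grades become available later and rest on stored images. The visible skin cue during joint counting remains, so ACR20 is only partly protected. The gain is one secondary outcome largely shielded from skin and visit cues.

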**Methods:**

This study will be an 8-week double-blinded, randomized, placebo-controlled clinical trial conducted at Guang’anmen Hospital in Beijing, China, and 168 patients with moderately active RA will be randomly assigned with a 1:1 ratio to apply a topical gel preparation containing TwHF or placebo. The primary outcome variable will be the proportion of subjects, by study group, to achieve a 20% improvement in the American College of Rheumatology criteria (ACR20) by week 8. Secondary outcome measures to be assessed at weeks 4 or 8 will include: measurement of ACR20 response rate at week 4, ACR50 response rate, the changes in DAS28 score, and joint synovitis classification assessment monitored by musculoskeletal ultrasound. Safety evaluations conducted at weeks 4, 8 and 12 will be based on spontaneous complaints by the study subjects, but special emphasis will be focused on cutaneous allergy and alterations of menstruation in premenopausal female participants. Statistical analyses will be performed using the intention to treat analysis data set.

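### The trigger for grading and attributing adverse effects is departure from a normal range, but the menstrual outcome is change from the woman's own pattern, so a change within normal limits need not be graded

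*Protocol article*

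**What the plan says.** The safety paragraph under Outcome measurements in the Protocol article does three things.

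- It names what is looked for. The adverse experiences of interest include "manifestations of cutaneous allergy (erythema, edema, itching) and gastrointestinal stimulation due to mucous membrane damage". Because of concern about reproductive toxicity, "the safety evaluation will focus on changes in menstruation patterns among premenopausal female participants". Routine blood and urine tests, with liver and kidney measures, "will be accomplished at baseline and on the 8th week".
- It says how menstruation is recorded. Whatever the woman answers to a general opening question, further questions try to "quantify any change in the menstrual cycle (extension, shortening or no change), or in the quantity of menstrual flow", the latter as increased, reduced or unchanged. Quantitative changes are to be put on record.
- It says when a judgment is written down. How severe an effect is, and whether it is linked to the gel, "will be documented if any of the above safety measures are observed to fall beyond normal clinical or laboratory ranges".

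The Methods part of the Abstract bases safety on complaints that participants volunteer at weeks 4, 8 and 12, and adds that "special emphasis will be focused on cutaneous allergy and alterations of menstruation in premenopausal female participants".

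**The concern.** The rule for grading and the definition of the menstrual outcome ask different questions. The rule asks whether a measure lies outside a normal range. The outcome asks whether the woman's own pattern has changed. Where the answers differ, a change that the trial set out to find may carry no severity and no causality judgment.

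This matters because menstruation is not incidental here. The Background gives reproductive harm from oral use as the reason for a topical route. The Discussion notes that earlier studies of the topical compound reported menstrual alterations, and it explains the four-week follow-up by the wish to cover a menstrual cycle. Severity and relationship are best judged at the contact itself, by someone who does not know the allocation. Judgments supplied later, if at all, may be less reliable, and may not be blind.

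**Working it through.** No arithmetic applies: the plan gives no figure on this point, and the rule depends on no rate, effect size or sample size. The check is to set the trigger beside each kind of safety information.

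**1. Two different tests.** Let c0 be a woman's cycle before treatment, c1 her cycle on treatment, and L to U whatever range is taken as normal (the article gives none).

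- Outcome: is c1 different from c0?
- Trigger: is c1 below L or above U?

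| Pattern | Outside L to U | Within L to U |
|---|---|---|
| Changed from c0 | Counted as a change; trigger met | Counted as a change; **trigger not met** |
| Unchanged from c0 | Not a change; range condition met | Not a change; trigger not met |

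The upper right cell is the gap. It exists for any L and U that leave room for more than one normal value, so it does not depend on a particular choice of limits.

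**2. What is recorded for menstruation.** The categories are cycle extended, shortened or unchanged, and flow increased, reduced or unchanged. All six are relative to the woman's own pattern and none states a level. An entry of reduced flow does not by itself show whether a normal clinical range has been left.

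**3. Item by item.**

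- *Skin and gastrointestinal signs.* Erythema, edema, itching and gastrointestinal irritation are abnormal by being present. The trigger speaks of clinical as well as laboratory ranges, and the clinical part reasonably covers them. No gap is shown.
- *Menstruation.* Gap as in steps 1 and 2.
- *Laboratory values.* A shift within the range is recorded but not graded. The plan does not name such shifts as a target, so this is a choice of threshold and not a contradiction.
- *Other volunteered complaints.* The Abstract bases safety on these, but the trigger refers only to the measures listed above it. A complaint outside that list has no stated route to grading.

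**4. When the gap applies.** There are three safety contacts: weeks 4, 8 and 12. Laboratory tests after baseline are taken only at week 8. At the other two contacts, grading rests wholly on the undefined clinical range.

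**5. What can be lost.** The follow-up questions are asked whatever the first answer, and quantitative changes are recorded. The change itself can therefore still be compared between arms. Only its severity and its attribution to the gel can be missing.

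**The case against.** The strongest reply has four parts.

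*An investigator may treat any reported change in pattern as clinically abnormal, and the sentence does not say that judgments are documented only then.* This is a reasonable reading, but the text does not settle it. A stated condition will tend to be followed as a condition.

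*The article condenses a fuller protocol, and the Quality control section refers to a standard operational protocol and a Case Report Form.* Grading scales and causality categories may well be there, and their absence is no fault. The point rests on a rule that the article does state. If the form grades every event, the sentence disagrees with the form; if the form follows the sentence, the gap is real.

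*No menstrual data are lost.* This stands, and it limits the point to grading and attribution.

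*Stronger readings do not hold.* A reader might infer any of the following:

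- That skin events also escape grading. This overlooks the clinical part of the trigger.
- That the plan neglects a targeted laboratory outcome. The emphasis in the Abstract is on skin and menstruation, and within-range laboratory shifts are nowhere named as a target.
- That unchanged baseline abnormalities will be tabulated as treatment effects. The sentence concerns adverse effects and their relationship to treatment, which is where a pre-existing finding would be set aside, and the article describes no such table.
- That the contrast between gel and placebo is diluted towards a finding of safety. The article describes no between-arm test of graded events, so this cannot be shown.

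**Conclusion.** The concern holds in a narrow form. The article fixes a rule based on level for documenting severity and relationship, while its emphasised menstrual outcome is based on change and has no stated range. As written, a menstrual change within normal limits, or a volunteered complaint outside the listed measures, would be recorded without necessarily being graded or attributed under the blind.

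The point is minor. Its frequency cannot be estimated, because the documents give no rate of menstrual change, no number of premenopausal participants and no range. The primary outcome and all efficacy comparisons are unaffected. The conclusion assumes that the sentence is applied as printed; a Case Report Form that already grades every event would reduce it to a correction of wording.

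**What to change.** Reword the sentence under Outcome measurements, and the matching page of the Case Report Form, so that:

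- severity and relationship to the study gel are documented, while the assessor is blinded, for every reported adverse event, whether or not it is among the listed measures;
- the same is done for every menstrual change from the participant's own baseline pattern, in cycle or flow, without reference to a normal range;
- laboratory values outside the range are judged against the baseline value already collected, so that a new abnormality is told apart from one that was present before treatment.

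The cost is one sentence and one form page. The contacts and laboratory tests are already planned, so no visit or sample is added. Staff record slightly more at each contact, and more events, many of them probably mild, will be listed in both arms.
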